## Abstract

**Study registration:**

Number: ISRCTN15575518

## Introduction

### Rationale

The Royal Society defines research culture as “the behaviours, values, expectations, attitudes and norms of our research communities. It influences researchers’ career pathways, and determines the way that research is conducted and communicated” [1]. In recent years the positive research culture (PRC) agenda has gained traction worldwide, with Higher Education institutions (HEIs) actively pursuing equality, diversity and inclusion, while promoting positive behaviours such as open research, integrity and collegiality. Initial reviews discuss substantial problems for those working in research including a culture of overworking, low job security, and nonoptimal work conditions and practices (e.g., bullying and harassment) leading to poor mental-health and wellbeing among working staff [2]. Funders and other stakeholders are calling on the sector to address these issues and build a more positive research culture in which staff can thrive, and there is a growing realisation that failure to further this agenda will ultimately compromise both staff wellbeing and research output quality [3]. The rapidly accelerating drive to improve PRC is visible in its integration into the Research Excellence Framework’s assessment of People, Culture and Environment in 2029 [3], which will pressure HEIs to make widespread changes in policy and practice if they want to be competitive for research funding.

One way the sector has tried to facilitate such changes is through educational programmes and initiatives. A recent UKRI review identified 292 initiatives, largely aimed at researchers and those supporting research activities, existed to promote positive research culture behaviours and values as they are noted in the UKRI PRC Framework [4]. However, this review also highlighted that the effectiveness of such initiatives is largely unknown due to a lack of rigorous evaluation [4], with the recommendation that future initiatives need to strengthen this component. In a period in which the Higher Education sector is struggling financially, and resources to foster PRC are likely to be diminish [5], it is crucial that the PRC agenda is furthered with an evidence-based approach.

In response to this shift, Cardiff University developed Cynnau|Ignite. This programme sits within the university’s holistic plan to promote PRC, and is rooted in the belief that culture change cannot be forced through a top-down approach, but rather everyone can and should advocate for, and contribute to positive culture change. Cynnau|Ignite seeks to promote PRC by imparting the knowledge, skills, and leadership development necessary for learners to feel empowered to advocate for a more positive research culture. The programme will be piloted at Cardiff University during AY 2024/2025, and will incorporate theory-based evaluation into every area of the programme’s design and delivery to ensure rigour. Its design was informed by evidence showing that similar programmes, often using face-to-face training and team development, have been an effective method of achieving culture change within higher education [6] especially when supported by senior or management staff and appropriate resources and skills were imparted [7]. With the backing of university management, Cynnau|Ignite aims to test the strength of advocating for PRC as route for change, via developing positive attitudes, cultural norms, skills, and leadership potential in Teaching and Research (T&R), Research-only (R), and Professional Services staff, Technicians, and Specialists (PST/S) from all disciplines across the university, enabling them to enact and advocate for PRC.

Cynnau|Ignite encompasses a holistic multidimensional approach to PRC and consists of three streams including Research Culture, Research Skills, and Action Learning. The delivery of these streams will be tailored to T&R, R, and PST/S learners based on their role requirements. By fostering community engagement around PRC, the programme is expected to maximize holistic benefits for all learners and manifest in intention formation and behavioural enaction of PRC, as defined by the UKRI PRC Framework [4], leading to positive culture change across the institution [8]. Alongside this programme, a dedicated evaluation will investigate the acceptability, implementation, and effectiveness of Cynnau|Ignite and its ability to help foster PRC practices, empowerment and leadership development at Cardiff University. This evaluation will not only inform future iterations of Cynnau|Ignite at Cardiff University, but may also lead to a greater understanding of the effectiveness of PRC initiatives in the UK, and how HEIs could most appropriately invest resources to promote these changes.

Cynnau|Ignite’s evaluation, and elements of its design, are partially informed by Ajzen’s Theory of Planned Behaviour (TPB) [9]. While there is not yet a theory of organisational behaviour and culture change that fully underpins all the programme aims to achieve, literature review shows potential for TPB to inform and evaluate organizational change [10]. A meta-analysis by Sheeran et al. [11] demonstrated considerable experimental support for TPB constructs and their effectiveness in predicting health behaviour change, as well as organisational change, where employee attitudes have long been proven critical for the success of interventions [12,13]. According to the TPB, colleagues’ intentions to engage and champion positive RC practices and behaviours will be stronger if they have favourable attitudes towards PRC, perceive that significant others (e.g., colleagues, line-managers, senior management) expect them to engage in PRC (norms), and think they have the skills and resources to enact PRC (i.e., perceived behaviour control, PBC). Meta-analytic synthesis shows that such intentions are moderately predictive of actual behaviours [14]. Given its robust framework, comprehensive measurable constructs (attitudes, norms, control and intentions), and moderate predictive power, with intentions explaining approximately 22% of variance in behaviour [14] the TPB will be used in conjunction with the UKRI PRC Framework (which also encompasses an holistic and comprehensive conceptualisation of PRC) [4], to map elements of the Cynnau|Ignite programme design and evaluation.

### Objectives

The primary aim is to reach a conclusion about the impact of Cynnau|Ignite on PRC at Cardiff University. Underpinned by theory-based approaches and a mixed-methods multi-informants design, evaluation will test whether Cynnau|Ignite can be implemented as planned, investigate how learners and other stakeholders (Heads of School/line managers, senior management and delivery team) will engage with it, and measure change in learners’ PRC intentions and behaviours. Evaluation will address the following research questions:

How do relevant stakeholders (e.g., design and delivery team, learners, heads of school/line managers, senior management, advisory board) understand Cynnau|Ignite, the outcomes it creates, how, and in what contexts?How do relevant stakeholders evaluate Cynnau|Ignite and the outcomes it creates, and what factors (learners, organizational, programme) shape its perceived value?To what extent is it feasible to implement Cynnau|Ignite at Cardiff University and what are barriers and facilitators (learners, organizational, programme) to its implementation and adoption?To what extent is Cynnau|Ignite effective in promoting learners’ intentions and behavioural enaction of PRC practices at Cardiff University; and improving stakeholders’ perceptions of and organisational indicators of PRC at Cardiff University.

Based on these questions, we hypothesise:

Stakeholders will be able to describe, and in many cases may have helped define, the programme’s purpose, and how it seeks to create change. Expectations of the overall cost/benefit will differ based on perspective (e.g., Heads of School and line managers may perceive greater disruption resulting from Cynnau|Ignite, compared to the delivery team).All stakeholders will value the programme, while understanding that the learners’ ability to translate intentions to engage with PRC into actual behaviours will depend on barriers and facilitators they experienced throughout.Implementing Cynnau|Ignite at Cardiff University will be feasible and practical due to its bespoke nature and close alignment with university values. We expect that immersing learners in an environment which directly fosters Cardiff University’s PRC aims, with support from senior management, will facilitate adoption of the programme. Additionally, the iterative, adaptable and bespoke nature of this programme may increase the feasibility of its wider adoption, and potential implementation in other institutions. However, we predict it’s high-resource design will make implementation and adoption vulnerable to common barriers such as lack of time, financial and human resources.Cynnau|Ignite will be acceptable and effective in increasing learners’ intentions of PRC practices at Cardiff University, compared to a control group of staff who did not participate in Cynnau|Ignite. We expect this difference to be evident across multiple dimensions of the UKRI PRC framework targeted (specifically research integrity, open approach to research, communicating research, ensuring an inclusive work environment, building collegiality, and realising impact [4]). Finally, we expect learners’ enaction of PRC practices will have a ripple effect at organisational level, improving perceptions of and indicators of PRC at Cardiff University.

### Cynnau|ignite programme

Cynnau|Ignite consists of three streams, as depicted in Fig 1: Research Culture—aiming to foster positive attitudes and commitment towards PRC, Research Skills—helping to impart the knowledge and skills necessary to action and advocate for PRC, and Action Learning - supporting learners in developing bespoke practice projects or small award grant applications, with potential funding of up to £2000 to facilitate individual projects around the theme of positive research culture.

**Fig 1 pone.0319020.g001:**
[figure not shown]
Schematic chronologic representation of Cynnau |Ignite’s implementation and evaluation.

Three versions of the programme will be delivered, tailored to the career needs of Early Career Researchers (ECRs) on Teaching and Research (**T&R**: 2 cohorts of 32 learners), or Research-only (**R**: 1 cohort of 32 learners) career pathways, as well as Professional Services colleagues, including Technicians and Specialists (**PST/S**: 1 cohort of 32 learners) across all disciplines in the university. Details of each tailored programme can be seen in Fig 1.

Fig 2 presents Cynnau|Ignite’s streams, modules, and sessions as mapped against the dimensions of the UKRI PRC framework that are targeted by the programme. Module Learning Outcomes can be found in supplementary material.

**Fig 2 pone.0319020.g002:**
[figure not shown]
Cynnau|Ignite streams and modules, mapped against relevant dimensions of the UKRI Research Culture Framework.

The programme’s tailored training sessions are hypothesized to help learners promote positive values and attitudes towards PRC, develop a relevant skill set (research career development, leadership) leading to higher perceived efficacy in enacting PRC, and aid in the creation of a community of practice that normalises PRC. In turn, according to the Theory of Planned Behaviour these elements should lead to the creation of strong intentions to practice, and advocate for, PRC and its subsequent behavioural enaction, which is supported by the Action Learning stream of the programme. Learners’ enaction of PRC practices is also expected to lead to improvements in stakeholders’ perceptions of, and in organisational indicators of, PRC at Cardiff University.

Cynnau|Ignite will be run as an interactive programme and all members of the delivery team have experience with participant engagement and a background in designing and implementing training programs for leadership, research skills and/or culture. Except for the Influencing Change module, all content was designed by a network of internal Cardiff University specialists aided by contributors such as specialists or Heads of School, who have specific knowledge and skills pertaining to the session they have been asked to lead. However, Influencing Change will be delivered by an external provider, 64 Million Artists, due to their expertise in creative leadership and helping academics to raise their research ambitions and shape thriving university environments. This provider was able to take a part of their existing “Leading Researchers” programme and create bespoke content to meet the requirements of Cynnau|Ignite’s Influencing Change learning outcomes. Discussions between both parties demonstrated similarities in leadership ethos and partnering expectations, for example, enthusiasm about creativity, belonging, and meaningful connections. Compared to other external providers, 64 Million Artists were able to provide additional strengths mapping opportunities, as well as make all session dates within the budget expected.

The programme will primarily be delivered face-to-face, however online access will be provided if it is requested as a reasonable adjustment due to personal circumstances (considered on a case-by-case basis). All training sessions will be held in conference rooms, either within Cardiff University or at an external venue, and rooms will be large enough to accommodate 32 participants and several members of the delivery team. Each session will run from 9 am until 4.30 pm, inclusive of lunch and rest breaks, and all learners must commit to attend all modules during the application process, with some flexibility given for those who cannot attend a single date. Attendance will be monitored and recorded.

Throughout, learners will have access to a physical Cynnau|Ignite workbook, featuring materials which guide them through all individual and group activities for each module (e.g., values and self-leadership assessments), and an online Microsoft Teams channel, where learners will have on-demand access to PowerPoint slides summarizing each module, and related reading materials. Using this channel, learners will have the ability to interact with programme facilitators and others in their cohort and share PRC resources. Learners are not restricted from engaging in other PRC initiatives or training programmes on their own volition, both within and outside Cardiff University.

### Study design

This is a pre-registered (ISRCTN15575518), theory based, mixed-methods and multi-informants’ prospective pragmatic evaluation of Cynnau|Ignite. A pragmatic approach fits this evaluation because we aim to provide definite answers to high-priority (but not exhaustive) questions pertaining the Cynnau|Ignite programme, when it is being flexibly implemented at Cardiff University with little selection of learners and low bias control, and with limited resources for evaluation [15]. The evaluation is underpinned by the UKRI PRC Framework [4] and a Cynnau|Ignite Theory of Change, presented in Fig 3, which demonstrates how the programme is intended to work and the assumptions behind this theory. This study will consist of a process evaluation to investigate Research Questions 1–3 (as described above), and a quantitative evaluation of effectiveness to investigate Research Question 4.

**Fig 3 pone.0319020.g003:**
[figure not shown]
Cynnau|Ignite Theory of Change describing inputs, activities and anticipated short-term outcomes. Potential Moderators and Unintended Consequences are outlined in red.

The effectiveness quantitative evaluation (displayed alongside Cynnau|Ignite’s implementation plan in Fig 1) is a prospective evaluation with three assessment moments: within two weeks of the start of the programme (baseline – T1), and two weeks following the final session (short-term follow up – T2), then six months after the end of the programme (mid-term follow up – T3). Fig 4 presents the Participant Flowchart. All cohorts will complete the baseline and short-term follow up, with an additional mid-term follow up for the R-only cohort (as course timetabling allows). A control group of university staff who did not take part in Cynnau|Ignite will fill in the baseline and short-term follow up with a 6-month gap in between, which equals the shorter period of Cynnau|Ignite implementation across the three groups (i.e., for the PST/S group) and is therefore comparable with the baseline and short-term follow up assessments for the cohorts.

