### Recruitment

The Cynnau|Ignite programme brochure will inform staff they will be invited to participate in this evaluation study. Staff who apply and are selected for the programme will receive an invitation to participate in the research in their Welcome Pack. In the event Cynnau|Ignite exceeds recruitment targets eligible participants will be chosen to maximise representation across roles, schools and units, however if this is not possible, participants will be randomly selected. As such, recruitment for the Cynnau|Ignite participant group will begin on 1^st^ September 2024, and end 8^th^ January 2025 (dependant on cohort start date). Recruitment for the control group will begin 1^st^ September 2024 and run until 1^st^ July 2025 or until target numbers have been reached and will first target staff who indicates an interest in attending Cynnau|Ignite (e.g., request brochure) but do not apply or are not selected, via email invitation. If recruitment targets are not reached with this strategy, participants will be recruited more widely within the university using CU communication channels. All non-trainee participants (e.g., heads of schools) will be invited to participate via email.

All prospective participants will be signposted to the Participant Information Sheet and Consent Form, where they will be required to provide full written informed consent before taking part in this research. After providing consent, participants will be directed to the baseline survey.

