As this is a pragmatic trial that has been retrospectively fitted around Cynnau|Ignite’s design, there are some limitations. While the programme is tailored to specific groups of staff at Cardiff University, this tailoring is largely achieved on the basis of omission. T&R learners will complete the full training program, but those in R or PST/S groups will receive a truncated version. This complicates the study as groups will not receive equal amounts of training (i.e., active components will vary), therefore we cannot expect Cynnau|Ignite’s benefits to be consistent across groups. Analytically controlling for this issue will be challenging because recruitment will take place at different times for each group and there is no guarantee that participation and recruitment quotas will be met, therefore it will not be possible to create a matched control cohort based on career pathway. While the addition of a control group is itself beneficial, an unmatched control group presents more of a challenge separating the direct impact of Cynnau|Ignite from wider changes in the sector, happening at Cardiff University and throughout the UK during 2024/25. Additionally, several of the measures described in this study were purposely built for the study and are self-reported, which limits the validity of findings. However, the use of mixed methods, multi assessments, and multi-informants should allow for enough data triangulation to ensure overall validity. Despite these limitations, we feel this is a robust theory-driven evaluation which is well placed to determine the effectiveness of Cynnau|Ignite and its feasibility for use in promoting PRC practices at Cardiff University and further afield.

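### A six-month control interval matches only the shortest programme, so the Group-by-Time contrast mixes programme effect with elapsed time and possibly calendar period

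*Protocol article*

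**What the plan says.** **Interval.** Under Study design in the protocol article, controls "will fill in the baseline and short-term follow up with a 6-month gap in between". The reason given is that this length "which equals the shorter period of Cynnau|Ignite implementation across the three groups (i.e., for the PST/S group) and is therefore comparable" with the T1 and T2 assessments of the cohorts, without limiting that to one cohort. Learner T2 is set differently: it comes "two weeks following the final session (short-term follow up – T2"), so it moves with the length of each cohort's programme. The Discussion adds that "T&R learners will complete the full training program, but those in R or PST/S groups will receive a truncated version".

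**Calendar.** Under Recruitment, learner enrolment "will begin on 1^st^ September 2024, and end 8^th^ January 2025", depending on cohort start. "Recruitment for the control group will begin 1^st^ September 2024 and run until 1^st^ July 2025 or until target numbers have been reached". Consent leads straight to the baseline survey, so a control's enrolment date is in effect the T1 date.

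**Analysis.** Under Analytical methods, the primary outcomes are tested with Group (programme, control) and Time (T1, T2). Each of T&R, R and PST/S is also compared with the same control group. Neither elapsed time nor date is mentioned there.

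**The concern.** The control group is there to show how much intentions and behaviours would have changed without the programme. It does that only if learners and controls are observed for about the same length of time and over about the same period. An interval equal to the shortest programme gives that for the shortest programme alone. In the longer tracks, learners have extra months in which anything else at the university or in the sector can move their answers, and no control is observed for as long. If controls also start later, the two groups live through different events. The contrast uses T1 and T2 as labels, so it counts any such difference as programme effect, or lets it hide one. This touches the primary comparison, and unequal intervals cannot be undone once the surveys have been sent.

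**Working it through.** **Inputs from the protocol article**
- Learners: four cohorts of 32 (two T&R, one R, one PST/S), total 128. Controls: 96, at most 32 per career path (Participants).
- Control T1–T2: six months, the PST/S length (Study design).
- Learner T1: within two weeks of programme start. Learner T2: two weeks after the last session (Study design).
- Learner recruitment closes 8 January 2025; control recruitment closes 1 July 2025 at the latest (Recruitment).
- f = 0.15, power .90, α = .05 (Participants).

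Not given in the text: the T&R and R durations (Fig 1, not shown), any rate of background change, and the correlation between repeated measures.

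**1. The plan's power figure.** For a repeated-measures interaction, λ = f²·N·m/(1 − ρ). With two groups, m = 3, ρ = 0.5 (assumed) and N = 96 in total, λ = 0.0225 × 96 × 3/0.5 = 12.96 and power is 0.902. With m = 2, N = 119 in total is needed. The pooled T1–T2 contrast plans 128 + 96 = 224, for a power of 0.994, and 128 against 48 still gives 0.944. Precision is therefore not the issue in the pooled contrast, and more participants would not remove a bias.

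**2. Who is matched on interval.**
- PST/S: 32/128 = 25% of learners. Their interval is six months plus two weeks, give or take up to two weeks for T1, that is, six months to six months and four weeks. This is nearly matched.
- If only T&R, the full programme, runs longer: 64/128 = 50% of learners have a longer interval than any control.
- If R runs longer too: (64 + 32)/128 = 75%.

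**3. Calendar.**
- 8 January to 1 July 2025 = 174 days.
- The control window, 1 September 2024 to 1 July 2025, is 303 days; 174/303 = 57% of it falls after learner recruitment closes.
- A control enrolled on 1 July 2025 has T2 about 1 January 2026. A six-month track starting on 8 January 2025 has T2 about 22 July 2025 (8 July plus two weeks). These two observation periods would barely overlap.

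**4. Illustration of size (assumptions, not findings).** Assume 1–4 extra months in the longer tracks and background drift of 0.02–0.05 SD per month.
- Pooled bias = share × extra months × drift: from 0.50 × 1 × 0.02 = 0.01 SD to 0.75 × 4 × 0.05 = 0.15 SD.
- In a single longer track, without dilution: from 1 × 0.02 = 0.02 SD to 4 × 0.05 = 0.20 SD.
- At two time points, f = 0.15 corresponds to a difference in change of 4 × 0.15 = 0.6 SD, so the pooled bias is 2–25% of the design effect.
- Standard error of the difference in change at ρ = 0.5: √(2 × 0.5) × √(1/128 + 1/96) = 0.135. With no programme effect, the rejection rate Φ(b/SE − 1.96) + Φ(−b/SE − 1.96) runs from 0.051 (b = 0.01) to 0.199 (b = 0.15), against a nominal 0.05. With 48 controls (SE 0.169) it runs from 0.050 to 0.144.

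The low end is negligible and the high end is not. Drift in the other direction would mask an effect. The calendar mismatch is not included in these figures.

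**The case against.** The case for leaving the plan alone has real parts.

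- **Disclosure.** The study is declared pragmatic with low bias control. The Discussion admits staggered recruitment, an unmatched control group and difficulty "separating the direct impact of Cynnau|Ignite from wider changes in the sector, happening at Cardiff University and throughout the UK during 2024/25". That stands, but neither unequal intervals nor the late control window is named, and the claim of comparability is not qualified.
- **Late enrolment is a limit, not a schedule.** Control recruitment stops when the target is met and starts with staff who showed interest but did not apply or were not selected, most of whom should surface during learner recruitment. This stands: the calendar mismatch is permitted, not certain.
- **An analysis plan could adjust.** For baseline date, it could. For elapsed time, a covariate does not help: the gap is constant among controls and tied to programme version among learners, so the model would be extrapolating.
- **Matching by career path is said to be impossible.** That concerns building a matched cohort. Dating a control's second survey by career path needs no quota, and career path is already a recruitment stratum.

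A reader might also infer more than the document supports. That 75% of learners have a longer interval is not established, because R also receives a truncated version and its length is not in the text. The authors do not call wider change the main threat; it is one of several limitations. Nor is prior exposure to organisational ripple effects special to late controls: any control at the same university may be exposed, and the Discussion expects the full extent of such effects only in the long term.

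**Conclusion.** The point holds. Six months is comparable for PST/S and is not shown to be comparable for any longer version, which covers 50% of learners if only T&R runs longer and 75% if R does too. The 50% rests on reading PST/S as the shorter version and T&R as the full one. The pooled contrast and those for the longer tracks therefore confound programme effect with elapsed time; the PST/S contrast is largely spared this. Calendar confounding is possible in every contrast, by up to 174 days at baseline, but occurs only if control recruitment runs late. It would be tempting to attach a definite bias or a false-positive rate near 0.20. The document does not support that: drift and extra months are assumed, and neither size nor direction can be computed from what it gives.

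**What to change.** 1. Schedule each control's T2 at the programme length of his or her own career path (T&R, R or PST/S). Let the analysis compare like with like by including career path and its interaction with Time, since learners are split 64/32/32 and controls at most 32/32/32.
2. Give priority to control baselines within the learner T1 windows. Closing control recruitment altogether on 8 January 2025 is not the obvious choice: it would remove up to 174 of 303 recruitment days and put the target of 96 at risk under the expected 20–50% attrition.
3. Specify a repeat of the primary analysis without controls enrolled after the learner window, optionally adjusting for baseline date. Do not rely on an elapsed-time covariate.
4. If six months is kept for everyone, withdraw the comparability statement for the longer tracks and add unequal intervals and late control entry to the limitations.

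The cost is some extra scheduling and analysis, and slightly more control attrition at longer gaps. Comparisons within one career path rest on at most 32 controls and will be less precise.
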